## Abstract

**Background:**

Pharmacological treatment for osteoarthritis (OA) can be divided into two groups: symptom-modifying drugs and disease-modifying drugs. Symptom-modifying drugs are currently the prescription of choice for patients with OA, as disease-modifying drugs are not yet available in usual care. However, there has recently been a lot of debate about glucosamine sulphate (GS), a biological agent that is thought to have both symptom-modifying and disease-modifying properties. This assumption has yet to be proved.

The objective of this article is to present the design of a blind randomised clinical trial that examines the long-term symptom-modifying and disease-modifying effectiveness of GS in patients with hip OA. This trial is ongoing and will finish in March 2006.

**Methods/design:**

Patients with hip OA meeting the ACR-criteria are randomly allocated to either 1500 mg of oral GS or placebo for the duration of two years. The primary outcome measures, which are joint space narrowing (JSN), and change in the pain and function score of the Western Ontario McMaster Universities Osteoarthritis index (WOMAC), are determined at baseline and after two years of follow-up during the final assessment. Intermediate measures at three-month intervals throughout the trial are used to study secondary outcome measures. Secondary outcome measures are changes in WOMAC stiffness score, quality of life, medical consumption, side effects and differences in biomarker CTX-II.

## Background

Pharmacological treatment for osteoarthritis (OA) can be divided into two groups: symptom-modifying drugs and disease-modifying drugs [1]. Symptom-modifying drugs are at present the prescription of choice for patients with OA. Drugs in this group are: simple analgesics (such as acetaminophen) and non-steroidal anti-inflammatory drugs (NSAIDs). Both acetaminophen and NSAIDs are effective in relieving symptoms of OA. In more severe stages of the disease NSAIDs are more effective, however, they are also the cause of serious side effects [2].

Disease-modifying drugs (i.e. drugs which alter disease progression) are not yet available in usual care. Although there has recently been a lot of debate about some biological agents that are thought to have both symptom-modifying and disease-modifying properties, results from previous trials have not been convincing. Of these biological agents, glucosamine sulphate seems to be the most promising.

Glucosamine sulphate (GS) has been shown to be an effective symptom-modifying agent, with effect sizes ranging from moderate to high [3,4]. In four trials that compared GS and NSAIDs, GS was found to be as effective as, or slightly more effective than NSAIDs [4]. Together with the fact that no serious adverse events have been reported concerning GS [3,4] this implies that GS may be a good alternative to NSAIDs. However, due to publication bias and due to quality issues in the trials studying GS, it may well be that reported effect sizes are exaggerated. A more recent trial studying the effect of GS did not find a difference between GS and placebo [5]. Also, several other uncertainties exist concerning the symptom-modifying properties of GS. For example, most trials were only of short-term duration (e.g. mean 6.25 weeks [4]) and it is therefore not possible to draw conclusions about the long-term efficacy. Another problem is that the mechanism behind the improvement of symptoms due to GS is not known. If GS directly influences the remaining cartilage, it would seem plausible that the symptomatic effect is greater in people with mild to moderate OA than in people with more severe OA, because there is more cartilage remaining in the first group. However, this possible difference in effect between different stages of OA has not been tested yet in a randomised clinical trial (RCT). These uncertainties make further study into the magnitude of long-term symptom-modifying effects in different stages of the disease justified.

Concerning disease-modifying effects, two recent long-term (three years) trials in patients with knee OA did report some evidence that GS affected the progression of OA [6,7]. Progressive joint space narrowing in the narrowest medial compartment of the tibiofemoral joint was used to define progression of knee OA (as recommended by a task force of the OA research society [8]). Whereas joint space narrowing (JSN), had significantly progressed in the placebo groups, it had not in the groups that were taking GS. This implies that daily intake of GS acted against progression of OA. However, these results are controversial, because both trials lacked appropriate and standardised protocols for taking radiographs. Although it is not likely that this influenced the results much [9], it is necessary to reproduce them in a study with well-standardised protocols. These two long-term trials both looked at the effect of GS on knee OA, no trial has been or is being performed yet that looks at its effect on hip OA.

Based on the above, we designed a long-term trial to answer our main question: Does glucosamine sulphate favourably modify progression of osteoarthritis? Because there still is uncertainty about the symptom-modifying properties of GS we will also try to answer three secondary questions: Does GS have the same effects in all stages of OA? What is the long-term cost-effectiveness of addition of GS to usual care? And, does GS prevent the onset or progression of OA in the contralateral hip joint? Additional to these clinical questions, the data will be used to look at changes on cell-level caused by GS to learn more about its possible mechanisms of action. All results derived from this trial will be published using our International Standardised Randomised Controlled Trial Number (ISRCTN).

In this article we will present the detailed protocol of the trial. This trial is ongoing; at the moment all patients are included and have passed the first 9 months of the follow-up period.

## Methods/design

### Study design

This study is a randomised, blinded, placebo-controlled trial. All actors in this trial, who may cause bias, are blinded to treatment allocation: the patient, who is the assessor of the symptomatic outcomes, the researcher, who is the assessor of the objective outcomes, and the caregiver. The analyses will also be performed blind. The study design was approved by the Medical Ethics Committee at the Erasmus MC – university medical centre Rotterdam. All patients gave written informed consent.

### Patient selection

General practitioners in the Rotterdam area agreed to search their electronic medical record for patients diagnosed with hip OA and for patients with symptoms associated with hip OA (i.e. persistent hip pain in combination with NSAID use). These patients are contacted by their general practitioner and informed about the trial. For more information, patients can forward their contact details to the researchers. These patients then receive an extensive information folder containing all the information needed to make an informed decision about participation in the study. This folder has been reviewed and approved by the medical ethics committee.

The information folder also contains an informed consent form, which patients need to fill out if they want to participate in the study. Patients who give written informed consent are contacted by phone for a preliminary check of the inclusion and exclusion criteria. People meeting these criteria are invited to the research centre of Erasmus MC for a baseline-measurement, during which the criteria can be checked more precisely.

### In- and exclusion criteria

Patients are eligible for inclusion when they meet one of the ACR criteria for hip OA [10]. Patients that have already undergone hip replacement surgery or those on the waiting list for joint replacement are not included in the study. Neither eligible patients with a Kellgren & Lawrence (K-L) score of 4 [11], nor people with renal and/or hepatic disease, diabetes mellitus or a disabling co-morbidity are included. Finally, patients unable to understand Dutch questionnaires are excluded from participation.

### Sample size

The sample size was calculated primarily to detect clinically relevant differences in radiological progression of the affected joints between the two groups (treatment and placebo) after two years of follow up. To detect a difference of 0.25 mm in radiological progression (SD 0.5) between the intervention and placebo groups (power 80%, alpha 5%, one-tailed testing) after two years of follow-up, 63 patients with hip osteoarthritis are needed per group. These calculations are based on an average change of 0.33 mm in joint space (SD 0.5) during one year of follow-up of patients with hip osteoarthritis [12].

Fewer patients are needed to detect relevant clinical differences: to detect a difference of 25% in pain (Western Ontario McMaster Universities Osteoarthritis index (WOMAC)) with one-tailed testing, a power of 80%, and alpha 5% (Mean 4.83, SD 2.25 [13]) 55 patients per group are needed. To detect the same difference in function (WOMAC) (mean 4.81, SD 2.18 [13]) 51 patients are needed per group.

As we expect a 20% loss to follow-up, we need to include 150 patients. However, to create options for studying effect-modification by type and severity of osteoarthritis, we oversized this trial to 220 patients (110 in each group).

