### Analyses

The researchers will be aware of allocation to treatment A or B at the time of the statistical analyses, but will not know which group received GS and which group received the placebo. All analyses will take place after the trial has finished, no intermediate analyses will be performed.

Success of randomisation and normality of outcome measures will be checked before actual analyses are done. Differences in the primary outcome measures JSN and WOMAC (pain and function) between the intervention and placebo group will be analysed on the basis of the 'intention to treat' principle using linear regression models. Additionally a per-protocol analysis will be done. When it turns out that randomisation was (partially) unsuccessful, we will adjust for differences in prognosis. Using baseline characteristics, we can identify factors that influence outcome of the study. Factors that change the outcome with 10% will be regarded as confounders and will therefore be added to the regression-model.

A cost-effectiveness analysis will be performed from a social and a patient perspective, looking at differences in direct and indirect health care cost between the two groups (GS and placebo). If the trial does not show a difference in disease parameters (WOMAC) and quality of life (EuroQol) between the GS and the placebo group, the analysis will be reduced to a cost minimisation analysis. This form of analysis evaluates the efficacy of treatment based solely on direct and indirect costs. If the study does find a positive difference in disease parameter and/or quality of life a cost-effectiveness ratio can be determined with on the one hand the costs and savings and on the other hand the disease-specific parameters and also quality of life.

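### The sample sizes are labelled one-tailed at 5%, but 63, 55 and 51 per group are two-tailed figures, so the decision threshold is contradictory

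*Protocol article*

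**What the plan says.** The Sample size section of the protocol article gives three calculations, each with its inputs.

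- **JSN:** "To detect a difference of 0.25 mm in radiological progression (SD 0.5) between the intervention and placebo groups", with the test specified as "power 80%, alpha 5%, one-tailed testing) after two years of follow-up, 63 patients with hip osteoarthritis are needed per group".
- **WOMAC pain:** "to detect a difference of 25% in pain", "with one-tailed testing, a power of 80%, and alpha 5% (Mean 4.83, SD 2.25 [13]) 55 patients per group are needed".
- **WOMAC function:** "To detect the same difference in function (WOMAC) (mean 4.81, SD 2.18 [13]) 51 patients are needed per group". Sidedness, alpha and power are not restated here. They are naturally read as carried over from pain.

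Loss to follow-up comes in only after these three figures: "As we expect a 20% loss to follow-up, we need to include 150 patients". The trial was then enlarged to 220 patients, 110 per group, to allow study of effect modification.

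The Analyses section names linear regression by intention to treat for the primary outcomes and does not say whether the tests are one- or two-sided. The Sample size section is therefore the only place in the article that fixes the direction and level of the primary tests.

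**The concern.** Every input is printed, so the figures can be checked, and the one-tailed label does not lead to any of them. A one-tailed 5% test needs roughly a fifth fewer patients than a two-tailed 5% test at the same power. The printed numbers sit at the two-tailed level for all three outcomes.

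What is at stake is how a positive result is defined. One-tailed testing at 5% claims benefit once the one-sided p-value falls below 0.05. Two-tailed testing at 5% requires it to fall below 0.025 in that direction. For a result between the two, the label gives one answer and the arithmetic the other, for each of three primary outcomes.

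**Working it through.** **Inputs (all from the Sample size section).** Alpha 5%, power 80%, equal groups.

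- JSN: difference d = 0.25 mm, SD 0.5.
- Pain: d = 0.25 × 4.83 = 1.2075, SD 2.25.
- Function: d = 0.25 × 4.81 = 1.2025, SD 2.18. Alpha, power and sidedness are assumed to be as for pain.

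**Formula.** Patients per group n = 2 (z_α + z_β)² (SD/d)², with z_β = 0.8416. One-tailed: z_α = 1.645, so (z_α + z_β)² = 6.183. Two-tailed: z_α = 1.960, so (z_α + z_β)² = 7.849.

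**Step 1: try to reproduce the printed figures.**

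| Outcome | 2(SD/d)² | One-tailed n | Two-tailed n | Printed |
|---|---|---|---|---|
| JSN | 8.000 | 49.5 → 50 | 62.8 → 63 | 63 |
| Pain | 6.944 | 42.9 → 43 | 54.5 → 55 | 55 |
| Function | 6.573 | 40.6 → 41 | 51.6 → 52 | 51 |

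No printed figure follows from the one-tailed label. Two match the two-tailed calculation exactly, and the third is 51.6 rounded down. Using the t distribution instead of the normal changes little: 50.2, 43.6 and 41.3 one-tailed; 63.8, 55.5 and 52.6 two-tailed.

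**Step 2: power at the printed sizes.** Power = Φ(d / (SD√(2/n)) − z_α). For JSN at n = 63, d / (SD√(2/n)) = 0.5 × √31.5 = 2.806. One-tailed: Φ(2.806 − 1.645) = 87.7%. Two-tailed: Φ(2.806 − 1.960) = 80.1%.

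| Outcome (printed n) | One-tailed 5% | Two-tailed 5% |
|---|---|---|
| JSN (63) | 87.7% | 80.1% |
| Pain (55) | 87.9% | 80.4% |
| Function (51) | 87.3% | 79.5% |

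The stated 80% is recovered only in the two-tailed column.

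**Step 3: could dropout explain the gap?** Dividing the one-tailed sizes by 0.8 gives 50/0.8 = 62.5 → 63, 43/0.8 = 53.75 → 54 and 41/0.8 = 51.25 → 52, which is close to the printed values. But the article applies the 20% loss afterwards: 2 × 63 = 126, and 126 × 1.2 = 151, about the stated 150 (dividing by 0.8 would give 158). So 63 is the figure before inflation.

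**Step 4: power at the planned size.** 110 per arm less 20% leaves 88.

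| Outcome (88 per arm) | One-tailed 5% | Two-tailed 5% |
|---|---|---|
| JSN | 95.3% | 91.3% |
| Pain | 97.2% | 94.5% |
| Function | 97.8% | 95.5% |

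**Step 5: size of the disputed zone.** For JSN at 88 per arm, the standard error of the difference is 0.5 × √(2/88) = 0.0754 mm. One-tailed testing claims benefit from 1.645 × 0.0754 = 0.124 mm, two-tailed from 1.960 × 0.0754 = 0.148 mm. An observed difference between these values is the contested result. Its probability is 2.5% if GS has no effect, and about 95.3 − 91.3 = 4.0% if the true difference is 0.25 mm.

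**The case against.** The best defence is that the mismatch does no harm to the design. If testing is two-sided, 5% and 80% are both right and only a word is wrong. If testing is one-tailed at 5%, alpha is as declared and power is better than declared. The trial was also enlarged well beyond either requirement. All of this stands, and it limits the point to the decision threshold. It does not remove it, because the label and the numbers still define different tests.

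It can also be said that an article may leave the sidedness of the analysis to a fuller document. That is fair, and the silence of the Analyses section is not itself a fault. But the Sample size section does state a sidedness, and its own figures contradict it.

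Three stronger readings are tempting and are not supported.

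- **That blinded analysis rules out a one-tailed test.** A reader might infer this because the analysts "will not know which group received GS and which group received the placebo". It does not follow. The regression on groups A and B yields a signed difference, both one-sided p-values can be computed, and a direction fixed in advance is applied when the key is opened. Coding delays the reading of the tail but does not prevent the test.
- **That the stated error rate is wrong, or doubled.** The article openly declares 5% one-tailed. A 5% chance of a false claim of benefit is then the declared rate. The 2.5% per direction is implied by the arithmetic and is promised nowhere in the text.
- **That all three figures carry an explicit one-tailed label.** JSN and pain do. For function it is only implied.

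**Conclusion.** The point holds as an internal contradiction: the stated test and the stated sample sizes do not belong together. The label calls for about 13, 12 and 10 fewer patients per group than are printed (63 − 50, 55 − 43, 51 − 41), and three outcomes pointing the same way rule out rounding. The error is on the safe side for power, and nothing about recruitment needs to change. What remains is an unresolved threshold for claiming benefit, which matters only if a primary result falls between one-sided p of 0.025 and 0.05.

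This rests on the article's own differences and SDs, a comparison of two means in equal groups, a 25% difference taken as 25% of the printed mean, and function sharing the test settings given for pain. The function figure of 51 rather than 52 is a minor rounding matter, and function does not drive the sample size.

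**What to change.** In the Sample size section, replace one-tailed with two-tailed in the JSN sentence and in the WOMAC pain sentence, and change the function figure from 51 to 52. Test the primary outcomes two-sided at 5%, and record this before the treatment key is opened so that the threshold cannot depend on the result.

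The change is to wording only. No patients are added, and two-sided power at 88 per arm stays above the promised 80% for every primary outcome. The one real price is a stricter threshold for benefit than the one-tailed label would have allowed, which costs about 4 percentage points of power for JSN and 2 to 3 for pain and function at that size.

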### Current status

A total of 40 GP's were found willing to participate in the study. They sent a total of 600 letters to inform possible eligible patients of the study. We received 417 requests for additional information and thus sent an equal amount of information folders. Of these 417 people 250 returned a written informed consent. Eventually 222 people entered the study. Of the 28 people that did not enter the study, most did not meet the inclusion criteria and a few people changed their mind and withdrew their informed consent before randomisation.

We started including patients at the end of September 2003 and the last patient was included on March 15^th ^of 2004. This means the study will run until March 2006. The first results will be available around September 2006.

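### The two-year joint-space power calculation reuses a one-year SD of change without justification, so the stated 80% power for 0.25 mm with 63 per group is not supported

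*Protocol article*

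**What the plan says.** The Sample size section of the protocol article sets the target as follows: "To detect a difference of 0.25 mm in radiological progression (SD 0.5) between the intervention and placebo groups", with "power 80%, alpha 5%, one-tailed testing) after two years of follow-up", and concludes that "63 patients with hip osteoarthritis are needed per group". It then gives the origin of the inputs: "These calculations are based on an average change of 0.33 mm in joint space (SD 0.5) during one year of follow-up". The Radiographs section confirms that the outcome is the change in minimal joint space width between baseline and two years.

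On size, the section says "As we expect a 20% loss to follow-up, we need to include 150 patients". It then reports that "we oversized this trial to 220 patients (110 in each group"; the reason given is to allow study of effect modification by type and severity of osteoarthritis. The Current status section adds that "Eventually 222 people entered the study" and that recruitment has closed.

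**The concern.** The same SD, 0.5 mm, appears for one year of change in the source and for two years of change in the calculation. The protocol neither explains this nor tests it over a range.

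The SD of a change score has two parts. Measurement error from the two readings does not accumulate with time. Real differences between patients in how fast they lose joint space do. The Randomisation section stratifies by radiological severity and by localised or generalised disease, so the population is mixed and some real variation in rate is to be expected. If it is material, the two-year SD exceeds 0.5 and power for 0.25 mm is lower than stated.

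The Background section makes disease modification the main question, and joint-space change is the outcome on which the trial was primarily sized. A reader who takes the stated 80% at face value could give a non-significant joint-space result more weight than it can carry.

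**Working it through.** **Inputs from the Sample size section.** Difference Δ = 0.25 mm; SD = 0.5 mm; alpha 5%; power 80%; 63 per group; 110 per group planned; 20% loss. Evaluable patients: 110 × 0.80 = 88 per group. (With 222 entered and an even split, 111 × 0.80 = 88.8, so 88 still serves.)

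**Formulas** (normal approximation, equal groups):
- n per group = 2 (z_α + z_β)² SD² / Δ²
- power = Φ( Δ / (SD √(2/n)) − z_α )
- z_β = 0.8416; z_α = 1.960 two-sided or 1.645 one-tailed

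**The plan's own figure.**
- Two-sided: 2 × (1.960 + 0.8416)² × 0.25 / 0.0625 = 62.8, so 63.
- One-tailed: 2 × (1.645 + 0.8416)² × 0.25 / 0.0625 = 49.5, so 50.

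The stated 63 therefore reproduces only as a two-sided calculation, although the text says one-tailed. Both are shown below.

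**Range for the two-year SD (an assumption; the document gives none).** Let f be the share of the one-year variance, 0.25, that is measurement error.
- Independent yearly changes: two-year variance = 0.25 (2 − f). With f = 0, SD = 0.5 × √2 = 0.71.
- Constant patient-specific rates: two-year variance = 0.25 (4 − 3f). With f = 0, SD = 0.5 × 2 = 1.00.
- In both models the SD stays at 0.50 only if f = 1.

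The values 0.71 and 1.00 assume no measurement error and are the upper ends of their models. The value 0.60 is included as a moderate case.

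**Power for 0.25 mm and n needed for 80% power (two-sided / one-tailed).**

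| Two-year SD (mm) | 63 per group | 88 per group | n per group needed |
|---|---|---|---|
| 0.50 | 80.1% / 87.7% | 91.3% / 95.3% | 63 / 50 |
| 0.60 | 64.7% / 75.6% | 78.9% / 86.8% | 91 / 72 |
| 0.71 | 51.0% / 63.3% | 65.0% / 75.8% | 126 / 99 |
| 1.00 | 28.9% / 40.4% | 38.1% / 50.5% | 252 / 198 |

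**Largest SD that keeps 80% power**, from SD = Δ / ( √(2/n) (z_α + z_β) ):
- 63 per group: 0.501 two-sided, 0.564 one-tailed.
- 88 per group: 0.592 two-sided, 0.667 one-tailed.

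**What that demands of measurement error at 88 per group.** Setting the two-year variance equal to 0.592² = 0.350 or 0.667² = 0.445:
- Constant rates: f = (4 − 1.40)/3 = 0.87 two-sided; (4 − 1.78)/3 = 0.74 one-tailed.
- Independent yearly changes: f = 2 − 1.40 = 0.60 two-sided; 2 − 1.78 = 0.22 one-tailed.

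In three of these four cases, most of the cited variance has to be measurement error for the trial to keep 80% power.

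**Difference detectable with 80% power at 88 per group**, (z_α + z_β) × SD × √(2/88):
- Two-sided: 2.802 × 0.5 × 0.1508 = 0.21 mm at SD 0.50, rising to 0.42 mm at SD 1.00.
- One-tailed: 2.487 × 0.5 × 0.1508 = 0.19 mm at SD 0.50, rising to 0.37 mm at SD 1.00.

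**The case against.** A reader might infer that the stated power survives only if the spread does not grow at all in the second year. That is true only for 63 per group with a two-sided test (limit 0.501). Under the one-tailed test that the section names, 63 per group tolerates an SD of 0.564. The trial as enlarged tolerates about 18% growth two-sided (0.592 / 0.5) or 33% one-tailed (0.667 / 0.5). This part of the defence stands.

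The upper values of the range assume error-free radiographs, and 1.00 also assumes perfectly constant individual rates. Realistic values under these models lie lower. At SD 0.71 the shortfall under the declared one-tailed test is about 4 points (75.8% against 80%). If nobody were lost, 110 per group would give 74.6% two-sided and 83.6% one-tailed at that SD. This also stands, and it is why a range is given and not a single figure.

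The spread in this trial may differ from the cited cohort in either direction. Hips with a Kellgren-Lawrence score of 4 are excluded and scores below 2 admitted, and imaging is standardised with side-by-side reading. That leaves the true two-year SD unknown, but it does not justify using a one-year value for two years.

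The oversizing is only a partial answer. Its stated purpose is effect modification, and any of it used to cover a larger SD is no longer available for that purpose.

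Finally, nothing in the document says that a non-significant joint-space result will be read as absence of disease modification. The one rule triggered by a null finding, the reduction to cost minimisation in the Analyses section, depends on WOMAC and EuroQol. Misreading is a risk to guard against, not something the plan prescribes.

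**Conclusion.** The point holds as an unsupported planning input behind a stated power. A one-year SD is used for a two-year outcome, and the protocol does not defend the step. The claim of 80% power for 0.25 mm with 63 per group therefore lacks support. For the trial as run, with about 88 evaluable per group, 80% power is kept only if the two-year SD is at most about 0.59 mm two-sided or 0.67 mm one-tailed.

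Two stronger readings go too far. This is not a proven arithmetic error, since 63 follows from the stated inputs as a two-sided calculation. Nor do the documents show that the trial is underpowered, since they contain no two-year SD. The mismatch in time span is certain. The size of the loss depends on the assumed SD, equal groups, 20% loss and the normal approximation. The matter should be corrected, but it does not undermine the design or the treatment estimate.

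**What to change.** Enrol no further patients. Before the analysis begins, restate the Sample size paragraph so that it:

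1. states an explicit assumption for the SD of two-year change and the reason for it;
2. gives power for 0.25 mm and the difference detectable with 80% power, for about 88 evaluable per group, over SD 0.5 to 1.0 (detectable difference 0.21 to 0.42 mm two-sided, 0.19 to 0.37 mm one-tailed);
3. names the sidedness actually used, since 63 is the two-sided number and one-tailed testing gives 50;
4. says that a non-significant joint-space result will be judged by whether its confidence interval excludes 0.25 mm, and not taken as evidence of no effect.

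The cost is wording. The drawback is that the stated power becomes less favourable.

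### WOMAC pain and function are primary as two-year changes but appear to be sized on score-level SDs, so the printed 55 and 51 per group rest on an unstated correlation unless the baseline score is always in the model

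*Protocol article*

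**What the plan says.** The Methods/design part of the abstract lists among the primary outcomes "change in the pain and function score of the Western Ontario McMaster Universities Osteoarthritis index (WOMAC"), determined at baseline and after two years. Table 2 agrees: both scores are marked as primary at 0 and 24 months only.

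The Sample size section handles these outcomes in one short paragraph. It opens "Fewer patients are needed to detect relevant clinical differences". It then sets the target, "to detect a difference of 25% in pain", specifies testing "with one-tailed testing, a power of 80%, and alpha 5"%, and gives for pain "Mean 4.83, SD 2.25 [13]) 55 patients per group are needed". For function it says: "To detect the same difference in function (WOMAC) (mean 4.81, SD 2.18 [13]) 51 patients are needed per group". It states no SD of change and no correlation between baseline and 24 months. Joint space, in the paragraph before, is sized differently: its SD of 0.5 mm is attached to a change in joint space, and 63 per group result. The trial is then enlarged: "we oversized this trial to 220 patients (110 in each group").

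The Analyses section says "Differences in the primary outcome measures JSN and WOMAC (pain and function) between the intervention and placebo group" will be analysed by linear regression. Adjustment is conditional. It follows if randomisation proves wholly or partly unsuccessful, and a factor enters the model if it changes the outcome by 10%. The section does not say that the baseline WOMAC score is always included.

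**The concern.** A target of 25% only makes sense as a fraction of something, and here that is a mean near 4.8, which reads as a score level. The SD printed beside that mean then reads as the spread of scores between patients at one visit. The primary outcome is a within-patient change, whose SD may be larger or smaller, depending on how strongly a patient's two scores correlate.

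Two statements depend on this. One is the 80% power attached to 55 and 51 per group, which covers two of the three primary outcomes. The other is that the symptom outcomes need fewer patients than joint space, which supports letting joint space set the trial size. Neither can be checked for the outcome as defined without the missing correlation or a commitment to baseline adjustment.

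**Working it through.** **Inputs.** From the Sample size section: pain mean 4.83, SD 2.25; function mean 4.81, SD 2.18; target 25% of the mean; power 80%; alpha 5%; joint space difference 0.25 mm, SD 0.5, 63 per group; 20% loss; 110 per group after enlargement. Assumed: equal SDs at both visits, normal approximation, and a baseline to 24-month correlation ρ, which is varied because the document gives none.

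**1. The printed figures.** n per group = 2 × (z_alpha + z_power)² × (SD/d)², with z terms 1.960 + 0.842 two-sided or 1.645 + 0.842 one-tailed.

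- Pain: d = 0.25 × 4.83 = 1.2075. Two-sided 54.5, so 55 (printed 55). One-tailed 42.9, so 43.
- Function: d = 0.25 × 4.81 = 1.2025. Two-sided 51.6, so 52 (printed 51). One-tailed 40.6, so 41.
- Joint space: two-sided 63 (printed 63). One-tailed 50.

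The printed sizes are therefore two-sided results carrying a one-tailed label.

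**2. The same sizes for an unadjusted change.** SD of change = SD × √(2(1 − ρ)), so n is multiplied by 2(1 − ρ), which equals 1 at ρ = 0.5. To keep 80% power at the printed N, 2(1 − ρ) must not exceed N/n:

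- Two-sided: pain 55/54.5 = 1.009, so ρ ≥ 0.495; function 51/51.6 = 0.988, so ρ ≥ 0.506.
- One-tailed: pain 55/42.93 = 1.281, so ρ ≥ 0.36; function 51/40.64 = 1.255, so ρ ≥ 0.37.

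Each cell shows the n per group needed, then the power at the printed 55 (pain) or 51 (function):

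| ρ | Pain, two-sided | Function, two-sided | Pain, one-tailed | Function, one-tailed |
|---|---|---|---|---|
| 0.2 | 88; 60% | 83; 60% | 69; 72% | 66; 71% |
| 0.3 | 77; 66% | 73; 65% | 61; 77% | 57; 76% |
| 0.4 | 66; 73% | 62; 72% | 52; 82% | 49; 82% |
| 0.5 | 55; 80% | 52; 80% | 43; 88% | 41; 87% |
| 0.6 | 44; 88% | 42; 88% | 35; 93% | 33; 93% |

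**3. The comparison with joint space.** Under the same test the z terms cancel, leaving 2 × (SD/d)²: joint space 2 × (0.5/0.25)² = 8.00, pain 6.94, function 6.57. As change scores, pain and function are multiplied by 2(1 − ρ). Pain needs fewer patients than joint space only if ρ > 1 − 8.00/13.89 = 0.42, and function only if ρ > 1 − 8.00/13.15 = 0.39. This holds under either sidedness.

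**4. The trial as enlarged.** 110 × 0.8 = 88 evaluable per group.

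- Two-sided: pain 88/54.5 = 1.615, so ρ ≥ 0.19; function 88/51.6 = 1.705, so ρ ≥ 0.15.
- One-tailed: 88/42.93 = 2.05 and 88/40.64 = 2.17. Both exceed 2, so 80% is reached even at ρ = 0 (81% and 83%).

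At the 150 patients named before enlargement (150 × 0.8 / 2 = 60 per group), the thresholds are 0.45 and 0.42 two-sided, and 0.30 and 0.26 one-tailed.

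**5. Baseline score in the model.** The residual SD is SD × √(1 − ρ²), so two-sided n is 54.5 × (1 − ρ²) for pain and 51.6 × (1 − ρ²) for function. At ρ = 0.3, 0.5 and 0.7 this gives 49.6, 40.9 and 27.8 for pain, and 47.0, 38.7 and 26.3 for function. The maximum, at ρ = 0, is about 55 and 52.

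**The case against.** Five things can be said on the plan's side.

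- **The SDs are unlabelled and their source is cited, not shown.** This is correct. That they are score-level SDs is inferred from the 25% target on a mean near 4.8 and from the contrast with joint space. The inference is strong, but it is not stated in the document.
- **A flat statement that the power holds only if the correlation is at least 0.5 would be wrong.** A reader might infer this from the two-sided arithmetic. The document names a one-tailed test, under which the threshold is 0.36 to 0.37, and either threshold applies only to an unadjusted change.
- **Linear regression may include the baseline score, and an article can leave that to a fuller plan.** If so, no minimum correlation is needed and the printed sizes are conservative. This stands in part. However, the article is not merely silent: it gives an adjustment rule, and that rule is conditional, so the baseline score is not in the model by default.
- **The printed sizes are not shown to be wrong.** This stands. With no correlation given, 55 and 51 may be sufficient or more than sufficient. They are unsupported for the outcome as defined, not refuted.
- **WOMAC does not set the trial size.** This also stands. Joint space does, and the enlargement adds a wide margin, although its stated purpose was effect modification, not WOMAC power.

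**Conclusion.** The mismatch holds. The primary WOMAC outcomes are changes, while their sample sizes come from what read as score means and SDs, with nothing to link the two. For an unadjusted change with equal SDs at both visits, the stated 80% power and the comparison with joint space are both conditional on an unstated correlation. At ρ = 0.3, for example, power at the printed sizes would be about 65% two-sided or 76% to 77% one-tailed.

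A reader might go further and infer that the trial is underpowered for its symptom outcomes. The documents do not support that. With 88 evaluable per group, only a correlation below 0.15 to 0.19, tested two-sided, would bring power under 80%. What needs repair is the justification of 55 and 51, the sentence claiming that fewer patients are needed, and the one-tailed label on two-sided numbers. The practical weight is modest.

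**What to change.** Keep the change definition of the primary outcomes. In Analyses, state that the linear regression for WOMAC pain and function always includes the patient's baseline score, whatever the balance checks or the 10% rule show. Modelling the change or the 24-month score then gives the same treatment estimate, so no primary outcome has to be renamed.

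In Sample size, label 2.25 and 2.18 as score SDs if that is what they are. State that the numbers are two-sided, print 52 in place of 51 for function, and note that with baseline adjustment about 55 and 52 are upper limits at any correlation.

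If an unadjusted change score is preferred, restate both sizes with the SD of the two-year change, or with 2.25 and 2.18 multiplied by √(2(1 − ρ)) and ρ given. Qualify the sentence that fewer patients are needed accordingly. The restated sizes may then be less favourable than those printed.

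The cost is wording in two sections. The baseline scores are already collected, and no extra patients or measurements are needed. The model should be fixed before outcome data by treatment group are examined. That is still feasible, because follow-up is ongoing and no intermediate analyses are planned.
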